#### Patient population

Patients with NSTEACS will be managed with an invasive approach if the following pre-requisites are met: (i) palpable radial artery with normal Allen or oximetry tests, (ii) familiarity of the operator with the radial (≥ 100 transradial coronary procedures per year with a femoral crossover rate ≤ 4%) and femoral techniques using VCD (≥ 50 transfemoral coronary procedures per year with AngioSeal) and (iii) agreement of the operator to use the access route determined by the randomization process (Table 2).

**Table 2 T2:** Eligibility criteria

	
Inclusion criteria	Non-ST-segment elevation acute coronary syndrome patients (ischemic symptoms suspicious of non-ST-segment elevation ACS (unstable angina or non-ST-segment elevation AMI) defined as clinical presentation compatible with a new manifestation or worsening of chest pain characteristic of ischemia at rest or at minimum effort, lasting more than 10 minutes, and at least one of the following items: (a) ECG changes compatible with new ischemia (ST-segment depression of at least 1 mm, transient ST-segment elevation, ST-segment elevation ≤ 1 mm or T wave inversion > 3 mm in at least two contiguous shunts); (b) cardiac enzymes (CK-MB or troponin T or I) above the upper normality range limit; (c) patients > 60 years of age without ECG or myocardial necrosis marker changes; however, with previous documentation of coronary atherosclerotic disease, confirmed by previous hospitalization due to AMI, previous percutaneous or surgical myocardial revascularization procedure, significant coronary atherosclerotic disease confirmed by coronary angiography or positive functional test for myocardial ischemia)
	Intention to submit patient to an early invasive strategy consisting of coronary angiography immediately followed by PCI, when applicable, in the first 72 hours after admission
	Patient informed about the nature of the study and agreeing with its general terms and having signed the informed consent, as approved by the Research Ethics Committee of the respective center
	Patient eligible for coronary angiography and both radial and femoral PCI with the following pre-requisites: (a) palpable radial artery with the Allen or normal oximetry tests, (b) familiarity of the operator with the radial and femoral techniques using AngioSeal, (c) agreement of the operator to use the access route determined by the randomization process
Exclusion criteria	Less than 18 years of age
	Pregnancy
	Chronic use of vitamin K antagonists, direct thrombin inhibitors or oral factor Xa antagonists
	Hypersensitivity to antiplatelet and/or anticoagulant drugs
	Active bleeding or high bleeding risk (severe liver failure, active peptic ulcer, creatinine clearance < 30 mL/min, platelets count < 100,000 mm^3^)
	Uncontrolled systemic hypertension
	Cardiogenic shock
	Previous myocardial revascularization surgery with ≥ 1 internal mammary or radial artery graft
	Documented chronic peripheral arterial insufficiency preventing the use of the femoral technique
	Severe concomitant disease with life expectancy below 12 months
	Participation in drug or device investigative clinical trials in the last 30 days
	Indication of elective percutaneous coronary intervention to be performed at a moment different from immediately after coronary angiography
	Medical, geographic or social conditions impairing participation in the study or inability to understand and sign the informed consent term

#### Procedures

Patients admitted with NSTEACS who are scheduled for early invasive stratification by coronary angiography followed by PCI, when applicable, will be evaluated in terms of feasibility of both radial and femoral access procedures. After the evaluation, with the patient meeting all inclusion criteria and in the absence of exclusion criteria, the patient may be included in the study after signing the free and informed consent term.

Patients will be randomized for the radial or femoral technique with VCD using a randomized sequence obtained by computer algorithms and maintained in individual, opaque and closed envelopes to conceal the allocation process.

Both radial and femoral coronary angiography will be performed using the Judkins technique and 6-French diameter sheaths and pre-molded catheters for selective catheterization of the left and right coronary arteries, with the possibility to change the diameter of the devices at the operator’s discretion. PCI will be indicated when a lesion presumably responsible for the adjacent clinical event is identified, with a stenosis diameter severity ≥ 70% and a high probability of angiographic success; PCI is ideally performed immediately after coronary angiography and left ventriculography. Patients with multiarterial coronary disease will be submitted to PCI after agreement among the clinical cardiologist, interventionist and heart surgeon. Procedures will be performed according to recommendations and provisions of current guidelines.

#### Arterial homeostasis

##### Radial approach

The TR Band device (Terumo Medical Corporation, Tokyo, JP) will be applied to obtain homeostasis according to a previously validated protocol [31,32]. Immediately after procedure completion, the sheath is initially pulled by approximately 2 cm. The device is applied to the patient with the green marker (located in the center of the larger balloon) positioned exactly at the puncture hole to aid in the location, visualization and control of possible bleeding. The balloon is inflated with an adequate syringe injecting 15 mL of air with simultaneous and total sheath removal, resulting in the absence of active bleeding. From the fourth hour and at each subsequent hour (fifth and sixth hours), 5 mL of air is slowly removed, maintaining the balloon connected to the syringe and controlling the plunger with the thumb. If bleeding occurs during any stage of device removal, the volume of air needed for homeostasis is again injected, repeating the process 60 minutes later. If device failure occurs, homeostasis will be obtained using a compressive dressing with a porous elastic adhesive bandage (Tensoplast, Smith & Nephew, London, UK).

##### Femoral approach

The AngioSeal VCD, comprising an absorbable collagen sponge and absorbable polymer anchor with polylactic and polyglycolic acid connected by an absorbable self-adjustable suture, will be used for hemostasis. The device seals the arteriotomy hole between its two major components, the anchor and collagen sponge. Hemostasis is primarily obtained through mechanical means that is supplemented by collagen platelet aggregation-inducing properties. The device will be released according to the manufacturer’s recommendations. First, an insertion introducer together with a femoral artery arteriotomy hole locator will be positioned using a 0.035-inch-guidewire. Once blood reflow by the distal edge of the set is confirmed, the guidewire and insertion introducer are removed, keeping the arteriotomy locator in position. Next, the repair and hemostasis device are inserted through the locator, exposing the anchor in the intraluminal space. The retreat of this second set places the anchor against the internal puncture hole. Maintaining the retreat, the collagen sponge is then released in the external puncture hole at the same time that the anchor is sustained, resulting in effective and safe hemostasis by preventing intra-arterial collagen release. Total set removal is achieved using an absorbable suture wrapped in a plastic tube to manually compact the collagen sponge against the arterial wall. After the appearance of an opaque mark, the suture is cut, the compacting tube exerting compression may be removed, and the remaining suture is cut close to the skin. If the device fails, homeostasis will be obtained by manual compression. Patients will be allowed to walk immediately after the radial procedure, and one hour after bed rest in the supine position after the femoral procedure with AngioSeal.

Table 3 illustrates possible antithrombotic treatment. After successful PCI, anticoagulant therapy will be withdrawn. Drugs such as angiotensin-converting enzyme inhibitors or angiotensin receptor blockers, beta blockers and statins will be prescribed according to current secondary prevention guidelines.

**Table 3 T3:** Adjunct antithrombotic therapy

**Site**	**Emergency unit**	**Catheter lab**	**Coronary unit and/or ward**	**Home use duration**
**Drug**				
Aspirin	300 mg orally	No	100 mg per day orally	100 mg per day orally, indefinitely
Clopidogrel	600 mg orally	No	75 mg per day orally	75 mg per day orally, 12 months
Prasugrel	60 mg orally	No	10 mg per day orally	10 mg per day orally, 12 months
Ticagrelor	180 mg orally	No	90 mg twice daily orally	90 mg twice daily orally, 12 months
Enoxaparin	1 mg per kg SC	0.3 mg per kg IV if the last dose is 8 to 12 hours 0.5 to 0.75 mg per kg IV if the last dose is >12 hours	1 mg per kg SC twice daily	No
Fondaparinux	2.5 mg SC	85 UI per kg IV UFH or 60 UI per kg IV UFH if GPI is scheduled	2.5 mg/SC/day	No
Abciximab	No	Intravenous loading dose of 0.25 mg per kg	0.125 mcg per kg per min for 12 hours, IV, without using HNF	No
Tirofiban	No	Intravenous loading dose of 25 mcg per kg	0.15 mcg per kg per min for 12 to 18 hours, IV, without using HNF	No

GPI, IIb-IIIa glycoprotein receptor inhibitor; UFH; unfractionated heparin, IV, intravenous; SC subcutaneous.

Electrocardiogram (ECG), CK-MB and/or troponin, glucose, creatinine, sodium, potassium, blood count and coagulation tests shall be obtained before patient randomization. Biomarkers (CK-MB and/or troponin) shall be checked between 12 and 24 hours after the procedure. ECG shall be performed soon after the procedure and within 12 to 24 hours after the procedure or when a new ischemic event is suspected. Hemoglobin and hematocrit dosage will be required in the presence of vascular complications or bleeding. Vascular and systemic complications related to the arterial vascular access will be evaluated in the interval between procedure completion, hospital stay and the first 30 days of evolution, through a scheduled visit. Other outcomes will be considered until the 30 days of evolution, with late follow-up by a visit or telephone call regarding cardiovascular death, AMI or stroke, at 12 months.

#### Statistical analysis

The primary analysis of the study is a non-inferiority comparison between the radial approach and femoral approach using VCD to decrease vascular complications at the arterial puncture site, in all randomized patients, based on the intention-to-treat principle.

Estimating a vascular complication rate pre-specified in the primary outcome of approximately 3% for the radial technique [19,32] and 12% for the femoral technique [26-31] and determining a non-inferiority margin of 0.15 based on historical data [18,19] with an alpha level of 0.05 and a beta level of 0.10, the minimum estimated sample size per group was established as 97 individuals. Twenty additional patients may be added to the final population to correct any subsequent loss of follow-up. This non-inferiority margin was derived from a trial that demonstrate the benefit of radial approach on the reduction of major vascular complications (hazard ratio, 0.37; 95% confidence interval, 0.27 to 0.52) as compared with femoral approach [18]. The non-inferiority margin of 0.15 was chosen in order to avoid a loss of greater than half the lower bound of the 95% confidence interval (0.27). The non-inferiority of the femoral approach with VCD will be declared if the lower confidence interval limit of 95% of the difference of both techniques does not include the specified inferiority margin value.

Categorical data will be presented as frequencies and group percentage and will be compared by chi-squared or Fisher’s exact tests. Continuous variables will be expressed as means and standard deviation and will be compared by Student’s *t-*test. Statistical analyses will be performed using Statistical Package for the Social Sciences for Windows (version 16.0; SPSS, Chicago, IL, USA).

The study was approved by the Dante Pazzanese Institute of Cardiology ethical committee, predicting and validating the Santa Casa de Marília as a co-participating institution. No extramural funding will be used to support this work. The authors are solely responsible for the design and conduct of this study, all study analyses and drafting and editing of the paper.

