##### Secondary outcomes

Individual components of the primary outcome, hematoma < 5 cm, major bleeding unrelated to the puncture site or myocardial revascularization surgery, device success and crossover rate; cardiovascular death, AMI or stroke at 12 months of evolution.

Study outcome definitions are listed in Table 1. A committee of clinicians will adjudicate all primary outcomes.

**Table 1 T1:** Outcome definitions

**Term**	**Definition**
Major bleeding	Type 3 ((3a) bleeding with hemoglobin drop ≥ 3 and < 5 g/dL, or packed red cells transfusion; (3b) bleeding with hemoglobin drop ≥ 5 g/dL, heart tamponade, bleeding requiring surgical intervention or bleeding requiring intravenous inotropic drugs; (3c) intracranial hemorrhage; subcategories confirmed by autopsy, imaging examinations or lumbar puncture; intraocular bleeding with vision impairment) or type 5 bleeding ((5a) possibly fatal bleeding, (5b) definitive fatal bleeding), according to the Bleeding Academic Research Consortium definition [30].
Retroperitoneal hematoma	Defined as building up of blood in the retroperitoneal space, caused by common femoral artery puncture above the inguinal ligament, not obtaining an adequate hemostasis with consequent hematoma formation. It is clinically manifested by dorsal, loin or inguinal pain, hypotension and/or hematocrit drop. Its diagnosis has to be confirmed by abdominal ultrasound and/or CT.
Compartment syndrome	Defined as abnormal tissue pressure increase inside an osteo-fascial compartment (considering in this analysis the involvement of upper or lower limbs after arterial puncture), impairing nervous and muscular structure irrigation, characterized by paresthesia, continuous pain, hypoesthesia, edema and stiffening of the affected region, peaking with tissue necrosis and/or permanent functional injury if not adequately treated.
Hematoma	Defined as localized collection of extravascular blood adjacent to the vessel, located in the topography of the punctured artery used to perform the procedure.
Pseudoaneurysm	Defined as a neocavity delimited by tissues adjacent to the injured vessel, fed by continuous blood flow into and out, coming from the real lumen through a narrow neck connecting it to the inside of the cavity. Diagnosis is determined by the presence of a pulsating bulge close to the puncture hole and is confirmed by duplex scanning.

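### The stated non-inferiority rule uses the intention-to-treat set only, although access crossover is foreseen and moves that comparison toward non-inferiority

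*Protocol article*

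**What the plan says.** Under Statistical analysis, the primary comparison of radial access with femoral access plus closure device is made "in all randomized patients, based on the intention-to-treat principle". Non-inferiority is then declared from one 95% confidence limit for the difference, set against the margin. The article names no second analysis set for that decision.

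Three other places bear on adherence to the assigned access:

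- Secondary outcomes lists "device success and crossover rate", so both will be recorded.
- Patient population qualifies operators by yearly transradial volume "with a femoral crossover rate ≤ 4" per cent. It also requires the operator to accept the randomised route.
- Femoral approach gives the fallback for the closure device: "If the device fails, homeostasis will be obtained by manual compression".

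The sample-size text allows for loss to follow-up and makes no allowance for crossover.

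**The concern.** In a superiority trial, patients who do not receive their assigned treatment usually pull the arms together and make a positive claim harder. In a non-inferiority trial the same pull makes the claim easier. Here a radial patient who has to be completed by the femoral route carries femoral risk but is counted in the radial arm. The radial arm then looks worse and femoral access looks closer to it. A femoral patient completed by the radial route has the matching effect in the other arm.

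At stake is the trial's main claim. If femoral access with a closure device is truly worse by the full margin, a rule based on intention-to-treat alone accepts it as non-inferior more often than the nominal 2.5%. The published rule does not require a second analysis that would show this.

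**Working it through.** **Inputs from Statistical analysis**

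- Event rates: "approximately 3% for the radial technique [19,32] and 12% for the femoral technique [26-31"].
- Margin: "determining a non-inferiority margin of 0.15 based on historical data [18,19"], read as an absolute risk difference.
- Error rates: "with an alpha level of 0.05 and a beta level of 0.10". Sidedness is not stated. A two-sided 95% interval implies one-sided 0.025.
- Size: "the minimum estimated sample size per group was established as 97 individuals".

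**The plan's own figure.** With unpooled variance, n = (1.960 + 1.282)² × (0.12×0.88 + 0.03×0.97) / (0.15 − 0.09)² = 10.507 × 0.1347 / 0.0036 = 393.2, so 394 per group. The stated 97 is not reproduced. The nearest non-inferiority match puts 12% in both arms: 10.507 × 0.2112 / 0.0225 = 98.6, so 99. That is a separate problem. The check below takes 97 as given because it is the planned size.

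**Crossover model.** Let c1 be the radial-to-femoral and c2 the femoral-to-radial crossover proportion. Assume that a crossover patient has the event rate of the access actually used. With rates R and F by access used:

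- pR = R(1 − c1) + F·c1
- pF = F(1 − c2) + R·c2
- SE = √[pR(1 − pR)/97 + pF(1 − pF)/97]
- P(declare non-inferiority) = Φ((0.15 − (pF − pR))/SE − 1.960)

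**Truth at the margin by access used (R = 0.03, F = 0.18)**

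| c1 | c2 | pR | pF | Difference | SE | False non-inferiority |
|---|---|---|---|---|---|---|
| 0 | 0 | 0.030 | 0.180 | 0.150 | 0.0427 | 2.5% |
| 4% | 0 | 0.036 | 0.180 | 0.144 | 0.0434 | 3.4% |
| 4% | 4% (assumed) | 0.036 | 0.174 | 0.138 | 0.0429 | 4.6% |
| 10% (assumed) | 0 | 0.045 | 0.180 | 0.135 | 0.0443 | 5.2% |
| 10% (assumed) | 10% (assumed) | 0.045 | 0.165 | 0.120 | 0.0432 | 10.3% |

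Second row in full: 0.006/0.0434 = 0.138; 0.138 − 1.960 = −1.822; Φ = 0.034. Only this row uses a crossover figure found in the article, and there it is a ceiling for operator qualification.

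**At the planning rates (3% versus 12%).** With c1 = 4%, pR = 0.0336. The difference moves from 0.090 to 0.0864, and the chance of declaring non-inferiority moves from 36% to 39%.

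**Closure-device failure.** A failed device leaves the patient on femoral access with manual compression, so no radial risk enters the femoral arm. If manual compression carries the same rate, nothing changes. Now assume 5% failures with a 25% event rate, and truth otherwise at the margin. Then pF = 0.18 + 0.05 × (0.25 − 0.18) = 0.1835, the difference is 0.1535, and false non-inferiority is 2.1%. The movement is away from non-inferiority.

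**The case against.** Five points can be made on the other side.

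1. *The article is condensed.* A supportive per-protocol set may stand in a full protocol or analysis plan that is not shown. This stands in part. A reader might infer that the trial has no check at all, and the article cannot establish that. It does state a complete rule for declaring non-inferiority, however, and under that rule intention-to-treat alone carries the claim.

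2. *Device failure.* Because the article foresees device failure as well as crossover, a reader might infer that both dilute the difference. The femoral fallback does not support this: the patient stays on femoral access, and the difference is unchanged or widens against the femoral arm. Failure of the radial band could act in the other direction, but only if it raises radial complications, and no rate is given.

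3. *Size.* The 4% is a qualification ceiling for operators and not a forecast for the trial. Operators must also accept the randomised route, and patients need a palpable radial artery with a normal test. This stands, and the effect at the documented figure is modest.

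4. *Estimand.* If the question is the effect of assigning an access strategy, femoral complications after failed radial access are consequences of that assignment, and intention-to-treat answers the question without inflation. This is a fair reason to keep it primary. The error rates above apply only where the truth is defined by the access used.

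5. *Per-protocol bias.* Excluding patients after randomisation can introduce selection. In particular, a femoral set restricted to successful device deployment would remove failures from one arm only and could flatter femoral access. This stands and shapes the fix.

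**Conclusion.** The point holds for access crossover and not for closure-device failure. The stated decision rule uses the intention-to-treat set only, crossover is foreseen and recorded, and it biases that comparison toward non-inferiority. At 4% radial-to-femoral crossover, false non-inferiority at the margin rises from 2.5% to 3.4%, a relative rise of more than a third (0.034/0.025 = 1.37).

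This rests on four assumptions: an absolute margin of 0.15, a one-sided level of 0.025, 97 per group, and a crossover patient having the event rate of the access used. A reader might go on to infer a doubling or more of the error. The rows that show this (4.6% at 4% each way, up to 10.3% at 10% each way) depend on crossover rates that the article does not give, so they show sensitivity and are not expected values. The change is worth making but is not critical. The unreproduced sample size in the same section is the larger problem.

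**What to change.** - Keep intention-to-treat as the primary analysis. State that a complication at any puncture site counts against the randomised arm, so that a crossover patient with two sites is handled clearly.
- Add a per-protocol analysis of patients whose procedure was completed by the assigned access. Keep femoral patients with closure-device failure in the femoral arm. Use the same confidence interval and margin.
- Claim non-inferiority only if the two analyses are consistent. If a fuller plan already has such an analysis, write it into the declaration rule.

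**Cost.** Crossover is already recorded, so this is one more analysis. The joint requirement lowers power slightly. At the planning rates with 4% radial-to-femoral crossover, intention-to-treat alone has 39%. With about 93 of 97 radial patients left (97 × 0.96), the per-protocol SE is √(0.0291/93 + 0.1056/97) = 0.0374, and Φ(0.06/0.0374 − 1.960) is about 36%. Requiring both cannot exceed that. Power is already low at 97 per group for the separate sample-size reason. The per-protocol set may also carry selection bias, which is why it supports the primary analysis and does not replace it.

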In summary, different VCD, although not demonstrating a class effect, clearly provide more comfort to patients, decreasing hemostasis and bed rest time. However, the inconsistency of data proving their safety limits their routine adoption as a strategy to prevent vascular complications, requiring evidence through adequately designed randomized studies. The hypothesis of this investigation is that among NSTEACS patients submitted to an early invasive strategy and randomized to the femoral or radial approach, the percutaneous femoral vascular closure device would decrease the prevalence of vascular complications at the puncture site, thus fulfilling the non-inferiority criteria compared with radial access.

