## Conclusions

Despite the proven efficacy of the radial approach in reducing vascular complications at the puncture site, the femoral approach remains the preferred technique at many centers worldwide. The ARISE trial will help define the role of vascular closure devices as a bleeding avoidance strategy in patients with NSTEACS.

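### The 15-point non-inferiority margin is wider than the whole 9-point radial advantage the plan assumes, and its hazard-ratio derivation does not support it on the risk-difference scale

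*Protocol article*

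**What the plan says.** The Statistical analysis section of the protocol article assumes a primary-outcome rate of "approximately 3% for the radial technique [19,32"] and "12% for the femoral technique [26-31"]. It then proceeds by "determining a non-inferiority margin of 0.15 based on historical data [18,19"], "with an alpha level of 0.05 and a beta level of 0.10", and reports that "the minimum estimated sample size per group was established as 97 individuals".

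The margin is traced to one cited trial of radial versus femoral access, with a hazard ratio of 0.37 (95% CI 0.27 to 0.52) for major vascular complications. The value 0.15 is explained as preventing a loss of more than half of 0.27. The decision rule compares a 95% confidence limit for the difference between techniques with this margin.

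The Radial technique section gives the same trial's absolute rates as 1.4% versus 3.7%.

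Under Percutaneous vascular closure devices, the hypothesis is that the device "would decrease the prevalence of vascular complications at the puncture site, thus fulfilling the non-inferiority criteria compared with radial access". The Conclusions say "The ARISE trial will help define the role of vascular closure devices as a bleeding avoidance strategy in patients with NSTEACS". Both randomized arms are active strategies: radial access, and femoral access with the device. There is no femoral arm without the device.

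**The concern.** A non-inferiority margin should be the largest loss that still leaves the new strategy acceptable. It is normally smaller than the advantage the comparator is believed to have. Here it is larger than that advantage, so the verdict can be reached when femoral access with the device keeps none of the radial benefit the plan assumes.

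The stated derivation would be the natural defence, but it moves a number from a ratio scale to a difference scale.

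At stake is the primary conclusion. The stated rule can return a non-inferior verdict from data that also show significantly more complications with femoral access. A reader of the hypothesis could take that verdict as evidence that the device reduces complications.

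**Working it through.** **Inputs (Statistical analysis, unless noted).** Radial 3%; femoral 12%; margin M = 0.15 on the difference; alpha 0.05 (sidedness not stated); power 90%; 97 per group; hazard ratio 0.37 (0.27 to 0.52). From Radial technique: 1.4% versus 3.7%.

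**1. The plan's own sample size.** n = [p1(1−p1) + p2(1−p2)] × (z₁₋α + z₁₋β)² / M².
- With 12% in both arms and one-sided 0.025: 0.2112 × 10.507 / 0.0225 = 98.6, so 99. This is within two patients of the stated 97.
- With 3% versus 12% and the 9-point difference counted against the margin, the same formula, with (0.15 − 0.09)² as denominator, needs 394 per group.

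So 97 is consistent with a two-sided 95% interval and no true difference. That interval is used below.

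**2. Margin against the assumed effect.**
- Assumed radial advantage: 12% − 3% = 9 points; 15 / 9 = 1.67.
- Boundary with radial at 3%: 3% + 15 = 18%; 18 / 3 = six-fold.
- The plan's femoral rate: 12 / 3 = four-fold, inside the margin.

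**3. The derivation.**
- Half of 0.27 is 0.135, not 0.15.
- More importantly, 0.27 is a limit of a hazard ratio, not a difference in risk.
- The cited trial's absolute difference was 3.7% − 1.4% = 2.3 points; 15 / 2.3 = 6.5. That endpoint is narrower than the ARISE composite, so 2.3 is context and not a replacement margin.
- As a rough conversion, treat the hazard ratio as a risk ratio and 12% as the conventional femoral rate. The limit most favourable to radial then gives 12% × (1 − 0.27) = 8.8 points, and the other limit gives 12% × (1 − 0.52) = 5.8 points. Both are full effects, not halves, and both are below 15.

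**4. Probability of declaring non-inferiority.** Exact binomial sums, 97 per group, with success when the upper two-sided 95% limit of (femoral minus radial) is below 0.15. This mirrors the article's lower limit if its difference is radial minus femoral.

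| True radial / femoral | Wald | Newcombe |
|---|---|---|
| 3% / 9% | 0.75 | 0.65 |
| 3% / 12% | 0.40 | 0.30 |
| 3% / 18% (boundary) | 0.04 | 0.02 |

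**5. One result with both verdicts: radial 1/100, femoral 8/100.**
- Difference 0.07; SE = √(0.08×0.92/100 + 0.01×0.99/100) = 0.0289.
- Wald: 0.07 ± 1.96 × 0.0289 = 1.3 to 12.7 points.
- Newcombe, from Wilson limits 0.0411 to 0.1500 (femoral) and 0.0018 to 0.0545 (radial): lower 0.07 − √(0.0389² + 0.0445²) = 1.1; upper 0.07 + √(0.0700² + 0.0082²) = 14.0 points.
- Fisher's exact P = 0.035.

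Both upper limits are below 15 and both lower limits are above 0.

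**6. What 12% refers to.** The article does not say whether it is the rate with or without the device.
- If without, a device with no effect lies within the margin.
- If with, the four-fold excess the plan expects counts as non-inferior.

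**The case against.** Several stronger readings are tempting, and the documents do not support them.

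- *A device that does nothing would pass.* The rule uses a confidence limit, not the true rate. At a true 3% versus 12%, the trial passes only 30 to 40% of the time. At the 18% boundary it passes about 2 to 4% of the time. Lying inside the margin is not the same as being declared non-inferior. The reading also needs 12% to be the rate without the device, which is not stated; several of the sources cited for it are closure-device studies.
- *The article concludes that the device avoids bleeding.* The Conclusions say only that the trial will help define a role. The wording about a decrease is in the hypothesis alone.
- *Contradictory verdicts will be common.* At 3% versus 12%, a result that is both non-inferior and significantly worse has probability of about 13% (Wald) or 4.5% (Newcombe). Some near-limit examples depend on the method: 2/100 versus 10/100 passes by Wald (upper limit 14.5) but not by Newcombe (15.6). Such a result is possible under any non-inferiority margin.
- *The trial cannot answer its question.* An interval lying well inside the margin would still be informative about radial access versus femoral access with the device.

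These points limit the claim. None justifies a margin wider than the assumed advantage, and none repairs the derivation.

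**Conclusion.** The point holds in this limited form. The margin is 15 points against an assumed radial advantage of 9, and the published derivation does not justify it. A three-fold true rate (3% versus 9%) would be declared non-inferior 65 to 75% of the time, and the plan's own four-fold rate 30 to 40% of the time. One dataset can satisfy the criterion and show femoral access to be significantly worse, whichever of the two interval methods is used. Without a femoral arm lacking the device, meeting the margin does not demonstrate the hypothesised decrease.

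The probabilities assume 97 per group, a two-sided 95% interval, and the difference read as femoral minus radial with success below +15 points. The article names no interval method, so both are shown. The main conclusion does not depend on what 12% refers to.

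Because the primary claim is affected and the remedy is cheap, this should be corrected before the outcome is analysed.

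**What to change.** 1. Remove the hazard-ratio derivation, or re-express it on the risk-difference scale with the assumed rates shown, stating whether 12% is with or without the device.
2. State that a positive result means only that an excess of 15 percentage points or more with femoral access plus device has been excluded.
3. Make the risk difference (femoral with device minus radial) and its 95% confidence interval the main result, and name the interval method.
4. Add one condition: no non-inferiority or bleeding-avoidance claim is made if the lower 95% limit of that difference is above 0.
5. Take the word decrease out of the hypothesis, and describe the question as a comparison with radial access.

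Reporting the same interval against a stricter margin is optional. With about 100 per group it would have low power: as an illustration, a 4.5-point margin (half of 9) would need 302 per group even with 3% in both arms (90% power, one-sided 0.025).

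The cost is wording and one extra condition on an interval that is already planned. A positive claim becomes harder to reach. No extra patients are needed.
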